#### Sample size estimation

A total of 1.400 patients must be recruited to show the non-inferiority of the experimental arm (incidental irradiation) with an 80% of statistical power when we assume a 5-year recurrence rate of 15% in the control arm (intentional irradiation) [8], a 5% non-inferiority margin, a yearly dropout rate of 5%, and a fixed sample design. Despite the short follow-up period, the large number of patients to be included in the study will preserve the statistical significance of the survival rates and will be enough to evaluate differences in the toxicity rates.

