### Follow-up

Patients will be followed for up to 5 years after the intervention according to the visit schedule detailed in Table 1. In each visit, a physical examination and recurrence assessment will be performed. An image assessment will be requested every year after the intervention. Reasons for discontinuing follow-up must be reported.

**Table 1 Tab1:** Schedule of visits and assessments (dots) that will be performed during the 5-year follow-up period

Post-intervention (year)	1					2		3		4		5	
Post-intervention (month)	1	3	6	9	12	18	24	30	36	42	48	54	60
Acute toxicity	●												
Physical exam	●	●	●	●	●	●	●	●	●	●	●	●	●
Image evaluation of local recurrence					●		●		●		●		●
Survival and disease recurrence	●	●	●	●	●	●	●	●	●	●	●	●	●
Chronic toxicity	(Continuous recording)												
Co-medication, (adjuvant)	(Continuous recording)												

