#### Statistical analysis

Two sets of patients will be analysed: the intention-to-treat (ITT) group, which includes all randomized patients, to describe the baseline clinic-pathological patients’ characteristics; and the per-protocol subset, which includes patients who finish the intervention treatment as planned with all dosimetry data completed, for the endpoint. A descriptive analysis will be carried out reporting absolute and relative frequencies for all variables recorded and stratified by treatment group. Two analyses of the primary endpoint (disease-free survival rate) will be conducted. The confirmatory analyses will be carried out using a non-inferiority long-rank test in the ITT set of patients, which includes all randomized patients regardless of whether the treatment or follow-up are accomplished. A secondary explanatory analysis will be conducted in the per-protocol subgroup, which will include patients who will have finished the intervention treatment with all dosimetry data completed, by an adjusted Cox regression model using the covariates: centre, age at inclusion, tumour size, hormone receptor status, Her2 receptor status, and OSNA results. With regards to the secondary endpoints: the outcomes of loco-regional and distant recurrence will be analysed using the Cox approach, this time in the ITT set. Acute toxicity will be analysed by a chi-squared test comparing frequencies in both treatment groups. Chronic toxicity will be analysed by using Kaplan Meier curves and comparing them by a standard log-rank test. Interim analyses are planned when 85 events and 169 events will be reached.

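### 1,400 patients followed for at most 60 months give about 186 events and about 70% power for the planned log-rank test at one-sided 5% (58% at 2.5%), not the stated 80%

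*Protocol article*

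**What the plan says.** All the relevant statements are in the protocol article.

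- **Sample size estimation:** the recruitment target is put as follows: "A total of 1.400 patients must be recruited to show the non-inferiority of the experimental arm (incidental irradiation) with an 80% of statistical power". The control-arm rate is given as "when we assume a 5-year recurrence rate of 15% in the control arm (intentional irradiation"), the margin as "a 5% non-inferiority margin", and dropout as 5% per year, under a fixed design. Alpha, a hazard-ratio margin, an accrual period and a target number of events are not given.
- **Follow-up and Table 1:** "Patients will be followed for up to 5 years after the intervention". The last visit column is month 60.
- **Statistical analysis:** the confirmatory comparison of disease-free survival (DFS) is made "using a non-inferiority long-rank test in the ITT set of patients". On interim looks: "Interim analyses are planned when 85 events and 169 events will be reached".
- **Study design:** allocation is 1:1.

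**The concern.** The power of a log-rank test depends on the number of events. The article fixes everything that determines this number: sample size, event rate, dropout and the length of follow-up per patient. It also names the test. The stated power can therefore be checked, and it comes out well below 80%. The interim event counts point the same way, because they suit a design expecting roughly 250 events, far more than 60 months of follow-up per patient should produce.

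In a non-inferiority trial, too few events means a confidence interval too wide to exclude the margin even when the two arms are equivalent. The trial would then end without an answer on whether intentional nodal irradiation can be omitted.

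**Working it through.** **Inputs from the article:** N = 1,400, 1:1; 15% events by 5 years in the control arm; margin 5 percentage points (15% against 20%); dropout 5% per year; maximum follow-up 5 years; log-rank test.

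**Assumptions added here:** exponential event and dropout times; proportional hazards; true hazard ratio 1; one-sided alpha of 5%, with 2.5% as the alternative.

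**1. Margin as a hazard ratio.** ln(0.80)/ln(0.85) = 1.373, and ln(1.373) = 0.317.

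**2. Events needed for 80% power.** 4(z_α + 0.842)² / 0.317²:
- one-sided 5% (z = 1.645): 246
- one-sided 2.5% (z = 1.960): 312

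**3. Events expected.**
- Event hazard λ = −ln(0.85)/5 = 0.0325 per year.
- Dropout hazard δ = −ln(0.95) = 0.0513 per year.
- P(observed event by year 5) = λ/(λ+δ) × (1 − exp(−5(λ+δ))) = 0.3879 × 0.3423 = 0.1328.
- 1,400 × 0.1328 = 186 events.

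**4. Power with 186 events.** Φ(√(186/4) × 0.317 − z) = Φ(2.162 − z):
- one-sided 5%: 69.7%
- one-sided 2.5%: 58.0%

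Two simulations of the log-rank test against 1.373 with the 60-month cap agree: 3,000 trials gave 69.8% and 57.6%; 4,000 trials gave 69.6% and 58.5%.

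**5. Attempts to recover the plan's 1,400 and 80%.**

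| Variant | Events | Power, 5% | Power, 2.5% | What it departs from |
|---|---|---|---|---|
| As stated | 186 | 70% | 58% | nothing |
| No dropout, 15% in both arms | 210 | 74% | 63% | dropout |
| Events counted at 15%/20%, with dropout | 217 | 76% | 65% | equal arms |
| Events counted at 15%/20%, no dropout | 245 | 80% | 70% | dropout, equal arms |
| 20% in both arms, with dropout | 248 | 80% | 70% | the 15% rate |
| Difference in 5-year Kaplan-Meier DFS, SE 0.0204 | – | 79% | 69% | log-rank test |
| 5-year accrual, common close when the last patient reaches month 60 | 251 | 81% | 71% | 60-month limit |

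About 80% returns only at one-sided 5%, and only by dropping something the article states. No variant tried reaches 80% at one-sided 2.5% under the 60-month limit.

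**6. Interim looks.** 85 × 3 = 255 and 169 × 1.5 = 253.5, so the looks fit one third and two thirds of about 254 events. With 186 expected events, the second look falls at 169/186 = 91% of the information.

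**7. Size needed as designed.** 246/0.1328 ≈ 1,850 patients at one-sided 5%; 312/0.1328 ≈ 2,350 at 2.5%.

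**The case against.** The best defence is that 1,400 may be a correct answer to a slightly different question. The endpoint and the inputs are expressed as 5-year rates, and a comparison of 5-year Kaplan-Meier rates has 79% power at one-sided 5%. A log-rank design with four to five years of accrual and a common closing date gives about 240 to 251 events and 79% to 81%. On either reading the number is roughly right, and the fault lies in its mismatch with the stated test and visit schedule. The full protocol, which is not shown, may also define the analysis time differently.

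Part of this stands. The evidence does not show how 1,400 was obtained, and the defect is fairly described as a conflict between the sample size on one side and the test plus follow-up on the other. The defence does not rescue the stated power, because the article names the log-rank test and ends visits at month 60.

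Three further caveats are fair:

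- **Margin conversion.** The article states no hazard-ratio margin. Taking 20/15 = 1.333 gives 62% at one-sided 5%; taking the odds ratio 1.417 gives 77%. Neither reaches 80% with 186 events.
- **The total of 254 is inferred.** It would not be expected under the stated assumptions, but higher event rates than planned could produce it.
- **Accrual.** Current status of the trial reports 451 patients in five years, so 5-year accrual of 1,400 does not describe this trial. Slower accrual with a common close would give more events: 10 years would give about 301, and 87% or 79% power.

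**Conclusion.** The concern holds. With the article's own inputs, test and follow-up, expected events are about 186 against 246 needed at one-sided 5% (312 at 2.5%). Power is about 70% (58%). A truly non-inferior result would be missed in about 30% of trials (42%), not 20%.

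The exact percentages rest on an assumed alpha, exponential times and a proportional-hazards conversion of the margin. The conclusion that power falls short does not depend on these choices within the ranges examined: both alphas and all three margin conversions leave power below 80% at 186 events, and removing dropout altogether gives only 74% at one-sided 5% with the 1.373 margin. This needs correcting, because it concerns the power of the primary comparison.

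**What to change.** **Required.** In Sample size estimation, name the one-sided alpha and the hazard-ratio margin. Give the expected number of DFS events under the month-60 limit (about 186) and the power that follows (about 70% at one-sided 5%, 58% at 2.5%). State the event total to which the looks at 85 and 169 refer, and reconcile it with Follow-up and Table 1. This costs a few sentences.

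**Optional, to regain about 80% without more patients.** Both figures are for one-sided 5%:

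- Make the difference in 5-year Kaplan-Meier DFS the confirmatory test: 79% power (69% at 2.5%). This needs no extra data, but it changes the primary test in an open-label trial already under way. It should be made by amendment, without sight of results by arm, and with the reason recorded.
- Continue the existing recurrence and vital-status form after month 60 until the last patient reaches month 60: 251 events and 81% power with 5-year accrual (71% at 2.5%), more if accrual is slower. The cost is a yearly status form. Recruitment began in February 2015, so this must be settled before early patients leave follow-up.

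At one-sided 2.5%, the Kaplan-Meier option does not reach 80%; the second comes close (79%) only if accrual runs to about 10 years.

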#### Statistical analysis

Two sets of patients will be analysed: the intention-to-treat (ITT) group, which includes all randomized patients, to describe the baseline clinic-pathological patients’ characteristics; and the per-protocol subset, which includes patients who finish the intervention treatment as planned with all dosimetry data completed, for the endpoint. A descriptive analysis will be carried out reporting absolute and relative frequencies for all variables recorded and stratified by treatment group. Two analyses of the primary endpoint (disease-free survival rate) will be conducted. The confirmatory analyses will be carried out using a non-inferiority long-rank test in the ITT set of patients, which includes all randomized patients regardless of whether the treatment or follow-up are accomplished. A secondary explanatory analysis will be conducted in the per-protocol subgroup, which will include patients who will have finished the intervention treatment with all dosimetry data completed, by an adjusted Cox regression model using the covariates: centre, age at inclusion, tumour size, hormone receptor status, Her2 receptor status, and OSNA results. With regards to the secondary endpoints: the outcomes of loco-regional and distant recurrence will be analysed using the Cox approach, this time in the ITT set. Acute toxicity will be analysed by a chi-squared test comparing frequencies in both treatment groups. Chronic toxicity will be analysed by using Kaplan Meier curves and comparing them by a standard log-rank test. Interim analyses are planned when 85 events and 169 events will be reached.

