## Methods/design

### Study design

The OPTIMAL study is an open-label multicentre and international trial (NCT02335957) conducted in over 40 sites in Spain, Portugal, and Italy. Eligible patients will be randomized with a 1:1 allocation ratio to receive irradiation on breast, tumour bed, axillary and supraclavicular lymph node areas (intentional arm) or only on breast and tumour bed (incidental arm), as depicted in Fig. 1. Randomization by blocking within centres to minimize imbalance of treatments among centres will be performed using the online randomization software RANDI2 (www.dkfz.de; Heidelberg University) embedded in the electronic case record form (eCRF). All patients will have to provide their Informed Consent prior to the inclusion in the study.

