### Data collection and analysis

#### Data collection

The study data will be recorded in an eCRF (OpenClinica®, LLC). The demographic and clinical data requested is depicted in Table 2. Acute and chronic toxicity will be recorded according to the Common Terminology Criteria for Adverse Events v4.0 (CTCAE) [24] criteria. Specific follow-up outcomes will be assessed and registered during the visits scheduled as stated in Table 1.

**Table 2 Tab2:** Data collected in the electronic case record form

Panel in eCRF	Data recorded
Informed consent	Date
I/E criteria	Yes; not
Demographic data	Age at inclusion; Menstrual State
Comorbidities	If yes: specify
Cancer Histology and Receptors, SLN OSNA	Tumour grade; Tumour size (maximum diameter); P53 (%); Ki67 (%); Lymphovascular infiltration; Ductal Ca in situ; % Estrogenic receptors; % Progesterone receptors; HER2 receptor status; OSNA TTL of SLN
Previous medication (Adjuvant therapy)	Drug; Start date; Stop date
Type of surgery	Tumour surgery; date; Margins
Randomization	Treatment randomly allocated; Randomization date
Radiotherapy intervention	Patient completed the allocated treatment (If no: main reason); Start date; End date; Treatment gaps (If yes, reason); Dose per volume (Mean; Median; D95; D5; Volume) in the breast, tumour bed, supraclavicular and axillary levels I-III, and Internal mammary chain
Co-medication	Drug; Start date; Stop date
Survival and disease recurrence	Date of follow-up visit (If not performed, reason); Local recurrence; Regional recurrence (If yes: nodal level); Distant recurrence (If yes: organ); Vital status (if dead: date and cause)
Image evaluation of local recurrence	Technique; Local recurrence (if yes: Maximum diameter)
Physical examination^a^	Palpable breast tumour (if yes: size, skin infiltration, inflammatory carcinoma, satellite lesions); Palpable axillary nodes (if yes: size); Palpable supraclavicular nodes (if yes: size); Node staging
Acute and chronic toxicity	CTCAE term; Grade; Start date; Stop date; Status (recovered w/o sequels; death)

*eCRF* electronic case record form, *OSNA* One-Step Nucleic Acid Amplification, *TTL* total tumour load, *SLN* sentinel lymph node, *CTCAE* Common Terminology Criteria for Adverse Events

^a^Physical examination is conducted at follow-up visits. It is also addressed at baseline and radiotherapy sessions to confirm the compliance of eligible criteria. If suspicious LNs are detected, the patient will discontinue the study

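### The confirmatory ITT log-rank test is valid but, as written, uses none of the five baseline covariates already named and collected; a marginal covariate-adjusted version would give a modest gain in power

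*Protocol article*

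**What the plan says.** All references are to the protocol article.

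- **Statistical analysis, confirmatory test:** "The confirmatory analyses will be carried out using a non-inferiority long-rank test in the ITT set of patients". No covariate or stratification factor is attached to it.
- **Statistical analysis, adjusted model:** "A secondary explanatory analysis will be conducted in the per-protocol subgroup". This is a Cox regression "using the covariates: centre, age at inclusion, tumour size, hormone receptor status, Her2 receptor status, and OSNA results".
- **Data collection, Table 2:** the histology panel of the eCRF includes "Tumour grade; Tumour size (maximum diameter" and "HER2 receptor status; OSNA TTL of SLN", together with oestrogen and progesterone receptors. Age is in the demographic panel. All five patient and tumour covariates are therefore collected.
- **Study design:** "Randomization by blocking within centres to minimize imbalance of treatments among centres". Centre is the only balancing factor described.

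**The concern.** The article fixes the decisive test, lists the covariates its authors want in a DFS model, and then places them only in a secondary analysis of a subset. Nothing described in the design or the confirmatory analysis uses these five covariates to reduce the variance of the primary comparison.

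What is at stake is precision. Current status of the trial reports 451 patients in five years, about 90 a year, against a target of 1,400. At that pace, information already held in the eCRF is worth using if it can be used without changing the question or the margin.

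**Working it through.** **Inputs from the document.** Sample size estimation gives 1,400 patients, 80% power, a 15% five-year event rate in the control arm, a 5% margin and 5% yearly dropout. Study design gives 1:1 allocation. Follow-up gives up to 5 years. Statistical analysis gives interims at 85 and 169 events.

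**Assumptions.** Alpha is not stated; one-sided 5% is used. The margin is read as 15% against 20%, which gives HR = ln(0.80)/ln(0.85) = 1.373 and ln HR = 0.317. Event and dropout times are exponential, the true HR is 1, and everyone is followed for exactly 60 months. No prognostic strength is given, so a range is shown.

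**The plan's own figure.** Schoenfeld: 4 × (1.645 + 0.842)² / 0.317² ≈ 247 events. This is close to the 254 implied if the interims fall at one third and two thirds (85 × 3 = 255; 169 × 1.5 = 253.5). Dividing by a mean event rate of 17.5% without dropout gives 247/0.175 = 1,411. With the stated dropout and exactly 5 years for all, the same route gives 1,593 (mean of 15% and 20%) or 1,860 (15% in both arms). So 1,400 can be reached only through choices the article does not state. It is neither confirmed nor shown to be wrong.

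**Baseline power under the assumptions above.**
- Hazards: event −ln(0.85)/5 = 0.0325; dropout −ln(0.95) = 0.0513.
- Event probability over 5 years: 0.0325/0.0838 × (1 − e^(−5 × 0.0838)) = 0.1328.
- Events: 1,400 × 0.1328 = 186.
- Power: Φ(0.317 × √186/2 − 1.645) = 0.697.

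**Ordinary adjusted Cox model.** In 1,500 simulated trials per setting, the standard error of the log HR was 0.147 unadjusted and 0.147 adjusted. Power against 1.373 was 0.69-0.71 unadjusted and 0.69-0.70 adjusted. Adjustment moves the target to a conditional hazard ratio. With strong covariates, the same marginal margin then makes the test conservative: rejection at the margin was 0.026-0.029 instead of 0.05.

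**Marginal adjusted (augmented) test, 15% event rate.** The simulation used 4,000 trials per setting and five covariates whose linear predictor has SD 0.5, 0.75 or 1.0 (c-index about 0.64, 0.70, 0.75). Effective events are 186 divided by the variance ratio, and power follows from the formula above.

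| SD | Variance ratio | Effective events | Power (from 0.697) | Equivalent patients, 1,400 × (1/ratio − 1) |
|---|---|---|---|---|
| 0.5 | 0.969 | 192 | 0.709 | 45 |
| 0.75 | 0.928 | 200 | 0.725 | about 108 |
| 1.0 | 0.904 | 206 | 0.735 | 149 |

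Two further simulations gave ratios of 0.977/0.934/0.903 and 0.974/0.934/0.891. The second showed power moving from 69% to 70%, 70% to 73% and 69% to 73%. Pseudo-value regression for the 5-year difference gave 0.980/0.933/0.897.

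**From 254 events instead of 186.** Power is 0.811 unadjusted and 0.822, 0.836 and 0.844 with the ratios in the table.

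**Event rate of about 6%.** The reported 13 recurrences fit a rate of this order. If entry was uniform, 451 × 2.5 = 1,128 person-years; 13/1,128 = 0.0115 a year; 1 − e^(−5 × 0.0115) = 5.6%, and slightly more after allowing for dropout. At 6.2% and HR 1.373 about 77 events are expected. The variance ratios are 0.993, 0.976 and 0.948, worth about 10, 34 and 77 patients, and power moves from 0.399 to 0.400, 0.405 and 0.413.

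**The case against.** The strongest reply is that nothing here is wrong. An unadjusted log-rank test in all randomised patients is a valid confirmatory test, and a more efficient estimator is an option rather than a correction. That stands, and it sets the weight of the point.

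A reader might infer that chance imbalance in receptor status or tumour load would bias the result. It would not. Such imbalance is random and already covered by the test's error rate. With 700 per arm, the between-arm difference in a factor of 20% prevalence has SD √(2 × 0.2 × 0.8/700), about 2 percentage points.

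A reader might also infer that the plan rules out adjustment. The article never says so. An analysis plan that is not shown may stratify or adjust. However, naming covariates for the per-protocol model and none for the ITT test does suggest an unadjusted test.

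The gain also rests on assumed prognostic strength. Eligibility narrows the spread of risk (T1-T2, ductal histology only, tumour load 250-15,000 copies/µL), so the upper scenarios are harder to assume. This stands, and the result is therefore given as a range.

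Finally, an adjusted DFS analysis is already planned. It does not fill the gap, because it is secondary, is confined to the per-protocol subset, and is an ordinary Cox model.

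**Conclusion.** The point holds as a minor, optional improvement. As written, the confirmatory ITT test leaves five named and collected covariates unused, and a marginal adjusted test would use them without changing the hazard ratio targeted or the margin.

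The gain is about 1 to 4 power points at a 15% five-year rate, with variance down about 3-10%, and about 0 to 2 points at about 6%. These figures assume one-sided 5%, 60 months of follow-up for all, a margin of HR 1.373 and a true HR of 1. They depend on a prognostic strength that the documents do not supply.

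Two stronger readings are not supported. The precision is not free, because the method needs programming, fixed covariate coding and a rule for missing values. Nor would simply moving the planned Cox model to the ITT set recover it, because against the same hazard ratio margin that model gains nothing.

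**What to change.** In Statistical analysis, before any comparison of the arms:

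- State that the confirmatory ITT analysis is a covariate-adjusted (augmented) log-rank or score test for the marginal hazard ratio. Use age, tumour size, hormone receptor status, HER2 status and log OSNA tumour load, with the same margin and a robust variance.
- Do not enter the 40-plus centres as separate terms.
- If the margin is applied to the 5-year DFS difference, use the same covariates in a marginal adjusted analysis of that difference, for example regression on Kaplan-Meier pseudo-values.
- Use the same adjusted statistic at the 85- and 169-event interims.
- Give a simple rule for missing covariates.
- Keep the unadjusted log-rank test as a sensitivity analysis.

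If a fuller analysis plan already adjusts the test, it is enough to align the protocol wording.

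The cost is a few sentences, some programming and an estimator that is less familiar to readers. No new data or patients are needed.
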